**Pain**	
None	15
Mild, no limitations on recreational activities	10
Moderate, limitations on recreational, but not daily activities	5
Severe, limitations on recreational and daily activities	0
	
**Stiffness**	
None	15
Mild, occasional, no limitations on recreational activities	10
Moderate, limitations on recreational, but not daily activities	5
Severe, limitations on recreational and daily activities	0
	
**Calf muscle weakness (subjective)**	
None	15
Mild, no limitations on recreational activities	10
Moderate, limitations on recreational, but not daily activities	5
Severe, limitations on recreational and daily activities	0
	
**Footwear restrictions**	
None	10
Mild, most shoes tolerated	5
Moderate, unable to tolerate fashionable shoes, modified shoes tolerated	0
	
**Active range of motion (ROM) difference between ankles**	
Normal (<6°)	15
Mild (6°–10°)	10
Moderate (11°–15°)	5
Severe (>15°)	0
	
**Subjective result**	
Very satisfied	15
Satisfied with minor reservations	10
Satisfied with major reservations	5
dissatisfied	0
	
**Isokinetic muscle strength (score)**	
Excellent	15
Good	10
Fair	5
poor	0

* Maximum overall score 100. An overall score of 90–100 rates excellent, 75–85 is good, 60–70 is fair and <55 is poor.

#### Follow-up

Follow-up visits for assessment of primary and secondary endpoints will be scheduled every week during the first 7 weeks. Thereafter, follow-up visits will be planned at 3, 6 and 12 month. Any other consultation for complaints concerning the Achilles tendon area will be documented.

### Design of analysis

Results will be analysed according the intention tot treat principle.

#### Data analysis

The study groups will be compared for their baseline characteristics. The number of complications will be calculated for the primary endpoint. Distribution measures will be calculated for the secondary endpoints at the different moments of follow-up. Differences between groups for the number of complications and distribution of other endpoints will be calculated for each outcome measure with a 95% confidence interval. The study groups will be compared with the chi-square test for categorical outcome variables and the independent sample Student *t *test for continuous outcome variables. The dropouts and withdrawals will be summarized and analyzed by treatment groups. A listing of subject with withdrawal with the date and reasons for termination will be provided.

Because we standardised the intevention procedures we do not anticipate important differences between centers. So we do not stratify our primary analysis for center. However, when eventually differences may occur we will explore their effect in a secondary analysis (Mantel-Haenszel). All analysis in SPSS (SPSS Inc, Chicago Illinois).

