## Background

Controversy continues with regard to the optimal treatment for acute subcutaneous Achilles tendon (AT) ruptures. Treatment can be classified into operative (open or minimally invasive/percutaneous) and non-operative. Post operative splintage can be divided into cast immobilisation and functional bracing.

Traditionally open surgical repair of a ruptured Achilles tendon has been the first choice of treatment due to low re-rupture rates and the possibility for functional post-operative splintage [1-4]. But, 34% of patients treated with open repair suffer from complications other than re-rupture, especially wound infection and adhesions [1-5]. In general, the outcome after treatment of a re-rupture is poor, but results following treatment of a deep infection are devastating [6]. Therefore an effort should be made to prevent infectious complications. Many articles on different types of minimally invasive repair techniques (using limited incisions or performed percutaneously) of ruptured AT's have been published [7-14]. But to date, only two 2 randomized trials have been reported [4,15]. In Khan's review on randomized trials complications other than re-rupture were substantially reduced with percutaneous repair techniques but data were very limited. Data on complications using limited incision techniques are even more scant. As minimally invasive techniques differ it is hard to compare other techniques with these numbers. An advantage of most minimally invasive techniques is smaller scars and less damage to the delicate blood supply of the AT. Importantly, in most patients minimally invasive surgery does allow functional rehabilitation [7]. Patients treated by functional rehabilitation after operation rather than cast immobilisation are reported to have a shorter in-patient stay, less time off work and a quicker return to sporting activities. In addition, lower complication rates, including re-ruptures, are reported [1-5].

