The main advantage of conservative, i.e. non-operative treatment is elimination of wound complications and intra-operative sural nerve damage. Complications other than re-rupture are reported to reduce to 3% [5]. But, conservative treatment with cast immobilisation has shown to increase the re-rupture rate [1,5] and cast immobilisation induces delayed recovery due to calf muscle weakness as a result of long immobilisation of the ankle joint. In contrast, conservative treatment by functional bracing does allow immediate weight bearing, preventing calf muscle weakness and enabling fast recovery. In three studies conservative treatment of AT rupture with functional bracing did not result in increased re-rupture rates [16-18]. But since only one of these is a randomized trial [17], more high quality data from randomized prospective studies is needed. We hypothesized that compared to surgical treatment, conservative treatment with functional bracing will reduce the absolute risk of complications other than re-rupture with 30%.

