### Design of collection of data

#### Primary endpoint

complications other than re-rupture, i.e. infection, disturbed wound healing, sural nerve injury, scar adhesions, deep vein thrombosis and all other complications per treatment group.

During follow-up all complications will be documented by a surgeon or resident according to a standardised procedure using the definitions of complications presented in the Table 2. All complications will be included in the final analysis of results.

**Table 2 T2:** Definitions of complications used during follow-up.

**Complication**	**Definition**
Infection	Clinical signs of wound infection, i.e. redness, swelling, pain and functional impairment. Deep infection is defined as an infection beyond skin or subcutaneous fat needing surgical treatment in the operating theatre.
Disturbed wound healing	Keloid formation or hypertrophic scar, secondary wound healing, protruding PDS knot.
Sural nerve injury	Any sign of altered sensibility in the sural nerve area diagnosed by surgeon or surgical resident (using touch and pin prick test).
Scar adhesion	Clinical signs of adhesion of skin to underlying tissue layers. Clear wound retraction at ankle movement.
Deep vein thrombosis	Clinical and ultrasonographic signs of deep vein thrombosis of the ipsilateral lower leg.
Other complications	Any complication met during follow-up.

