#### Sample size

Sample size is calculated on the basis of complication other than re-rupture. With conservative treatment using this new type of functional bracing we hypothesized a 30% reduction in the absolute risk for complications other than re-rupture. This risk reduction is similar to the risk reduction obtained in the systematic review on open versus conservative treatment by Khan: risk of complications for open repair being 34% [5]. Prospective data on the risk of complications of minimally invasive repair is very scant. The Khan review provides the best empirical estimate for the complication risk associated with surgical repair. Therefore we decided to use this risk estimate of complications of open repair for the sample size calculation. With a one-sided α of 0.05, a statistical power of (1-β) of 0.80, and an attrition rate of 10% we need to randomize at least 36 patients per treatment arm.

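### The primary measure is stated as a number of complications, but the hypothesis and the 36 per arm rest on the risk per patient

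*Protocol article*

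**What the plan says.** All references are to the protocol article.

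- **Primary endpoint.** The endpoint is a list of complication types (infection, disturbed wound healing, sural nerve injury, scar adhesion, deep vein thrombosis, others), given per treatment group. The section adds: "All complications will be included in the final analysis of results". Table 2 defines each type, and nothing limits a patient to one.
- **Data analysis.** "The number of complications will be calculated for the primary endpoint". The contrast is also in that unit: "Differences between groups for the number of complications" are to be given with a 95% confidence interval. The named tests are chi-square for categorical outcomes and Student's t for continuous ones, with Mantel-Haenszel as a secondary analysis if centres differ.
- **Background.** The surgical rate is a share of patients: "34% of patients treated with open repair suffer from complications other than re-rupture".
- **Sample size.** The planned effect is a risk: "we hypothesized a 30% reduction in the absolute risk for complications other than re-rupture". From it the authors conclude that "we need to randomize at least 36 patients per treatment arm".

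No section defines the primary variable as patients with at least one complication.

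**The concern.** The trial is sized in one unit and its primary measure is written in another. Under the Table 2 definitions a single wound can score as an infection, then as secondary wound healing, then as a scar adhesion. Weekly visits for seven weeks, then visits at 3, 6 and 12 months, give ample opportunity to record such a sequence.

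Two things are at stake. First, a difference in the number of complications does not estimate the absolute risk difference in the hypothesis. Second, if the totals go into a two-by-two table, several events in one patient are counted as if they came from different patients. The standard error is then too small.

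The choice of unit should also not be left open in an open-label trial whose assessors can see the allocation, because it could be settled after the results are known.

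**Working it through.** **1. Unit behind the 36 per arm.** Inputs: p1 = 0.34 (Background, Sample size); p2 = 0.34 − 0.30 = 0.04; power 0.80; attrition 10%. The formula compares two proportions, with one yes/no outcome per patient:

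n = [z_α·√(2·p̄(1−p̄)) + z_β·√(p1(1−p1) + p2(1−p2))]² / (p1−p2)², with p̄ = 0.19.

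Two-sided 0.05: (1.960 × 0.5548 + 0.8416 × 0.5126)² / 0.09 = 1.5188² / 0.09 = 25.63.

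Continuity correction: (25.63/4) × [1 + √(1 + 4/(25.63 × 0.30))]² = 31.95, so 32. Attrition: 32/0.90 = 35.6, so **36**. The plan's figure is reproduced.

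The stated one-sided 0.05 gives 21 per arm (24 after attrition) without the correction and 27 (30) with it. That discrepancy is a separate matter. What counts here is that 36 comes from a formula for patients, not events.

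**2. What an event count would estimate.** With m complications per affected patient in both arms, the difference in events per patient is (0.34 − 0.04) × m. The documents give no value for m, so these are assumptions:

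- m = 1.0: 0.30
- m = 1.1: 0.33
- m = 1.5: 0.45
- m = 1.7: 0.51

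The two measures agree only at m = 1. If m differs between arms, the event difference also mixes risk with multiplicity.

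**3. Type I error if totals are tested as if they were patients.** Let k be the number of complications in an affected patient and p the share affected. The true variance of a patient's count is p·E(k²) − (p·m)². A chi-square on totals over patients assumes pm(1 − pm). A test on the split of the total assumes pm.

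Example: p = 0.25, with k = 1, 2, 3 at probability 0.6, 0.3, 0.1. Then m = 1.5 and E(k²) = 2.7.

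- True variance: 0.675 − 0.141 = 0.534.
- Totals over patients: assumed 0.375 × 0.625 = 0.234, ratio 2.28. The cut-off of 1.96 acts like 1.96/√2.28 = 1.30, a two-sided error of about 19%.
- Split of totals: ratio 0.534/0.375 = 1.42. The cut-off acts like 1.64, about 10%.

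Simulation with no true difference, 32 per arm, two-sided 5%, 100,000 replicates per scenario:

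| Affected | k = 1/2/3 | m | Totals over patients | Split of totals | Patients with at least one |
|---|---|---|---|---|---|
| 25% | 1/0/0 | 1.0 | 5% | 2% | 5% |
| 25% | 0.9/0.1/0 | 1.1 | 8% | 4% | 5% |
| 25% | 0.6/0.3/0.1 | 1.5 | 21% | 11% | 5% |
| 15% | 0.5/0.3/0.2 | 1.7 | 22% | 15% | 5% |
| 30% | 0.5/0.3/0.2 | 1.7 | 29% | 12% | 5% |

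Over 15% to 30% affected and m from 1.1 to 1.7, the ranges are about 8% to 29% and about 4% to 15%. One-sided at 5%, the 25%, m = 1.5 scenario gives about 14% and 8%. A t test on per-patient counts stays near 5% throughout.

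**The case against.** The strongest reply is that no sentence applies the chi-square test to complication totals. The Data analysis section compares study groups, which consist of patients, and a categorical outcome gives one category per patient. The hypothesis in absolute risk, the intention-to-treat principle and the Mantel-Haenszel analysis all fit a table of patients, so the number of complications may be shorthand for patients with a complication. The sentence on including all complications may mean only that no type is left out. A literal count per patient could also go to the t test, which holds its level.

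Much of this stands. A reader might infer that the primary test as written is invalid and that its error rate exceeds 5%. The documents do not support that. It needs one particular application of the test, which is implied but not stated, and a multiplicity that the documents do not give. With few repeat complications the inflation is small, or absent for the split of totals.

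The reply does not remove the mismatch. The patient reading is possible, but it is not written, and both the summary measure and the contrast are worded as counts. Nor is this only an article leaving detail to a fuller document: the article itself states the measure, the contrast and the sample-size basis, and the first two do not match the third.

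**Conclusion.** The point holds as a mismatch of units in the trial's only primary comparison. The stated measure counts complications, while the hypothesis and the 36 per arm count patients. An event count would not estimate the risk difference for which the trial was sized unless every affected patient had exactly one complication. This conclusion comes from the text and needs no assumption about multiplicity.

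Type I inflation is a conditional consequence. It arises only if totals are entered in the chi-square or Mantel-Haenszel table, and the ranges above rest wholly on the assumed share of patients affected and the assumed complications per affected patient. They show what the ambiguity could cost, not what the plan's test will do.

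**What to change.** In the Primary endpoint and Data analysis sections, define the primary variable as the proportion of patients with at least one complication other than re-rupture within 12 months of follow-up. Apply the chi-square test, the 95% confidence interval for the risk difference and any Mantel-Haenszel analysis to patients. Report total complications and each complication type by arm as descriptive results.

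This changes wording only. It needs no new data, and 36 per arm is unchanged because that figure already assumes one yes/no outcome per patient. The cost is that the primary test no longer reflects several complications in one patient. That burden then appears only in the descriptive tables.

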## Methods/Design

### Design of study

#### Context

The efficacy of minimally-invasive surgery versus functional conservative treatment of acute subcutaneous Achilles tendon ruptures will be studied in a randomized trial. Four hospitals in the Netherlands will participate in the study, one of them being a university medical centre. The Medical Research Ethics Committee of all the participating hospitals approved the study protocol.

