#### Randomisation and concealment

Randomisation is concealed by a specially designed internet site. Randomisation is in blocks (4 blocks) and stratified by centre. The treatment nature is open labelled for patients, physicians and physiotherapists. During follow-up visits physical examination reveals the allocated treatment to patient and assessor.

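### Randomisation is stratified by centre but the primary chi-square ignores centre: conservative if centres differ strongly, and avoidable at almost no cost

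*Protocol article*

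**What the plan says.** Under Randomisation and concealment, the protocol article states: "Randomisation is in blocks (4 blocks) and stratified by centre". Under Context: "Four hospitals in the Netherlands will participate in the study".

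Under Data analysis, the test for the primary endpoint follows from the general rule: "The study groups will be compared with the chi-square test for categorical outcome variables". Group differences "will be calculated for each outcome measure with a 95% confidence interval".

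The same section addresses centre directly. The reason comes first, "Because we standardised the intevention procedures we do not anticipate important differences between centers", then the decision, "So we do not stratify our primary analysis for center", and then a conditional addition: "when eventually differences may occur we will explore their effect in a secondary analysis (Mantel-Haenszel)". The article does not say what counts as a difference between centres or how it would be detected.

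**The concern.** Stratified block randomisation forces the arms to be nearly balanced within each hospital. Variation between hospitals then largely cancels out of the treatment comparison. A pooled chi-square computes its variance as if that variation were still present. When centre predicts the outcome, the standard error is too large for the design, the test rejects less often than its nominal level, and the interval is wider than it need be.

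The stated reason covers only part of the question. Standardised treatment does not by itself equalise case mix or the threshold for recording a complication. One of the four hospitals is a university centre, both surgeons and residents operate, and assessment is open. Some definitions in Table 2, such as those for sural nerve injury and other complications, leave room for judgement. Centre differences are therefore possible, though the documents do not show that they will be large.

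At stake is some precision in a small trial, and whether readers will always see the centre-adjusted result.

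**Working it through.** **Inputs from the protocol article.** Four centres; 34% complications with surgery and a 30-point absolute reduction, so 4% with conservative treatment; 36 randomised per arm; 10% attrition (Sample size). Evaluable per arm: 36 × 0.90 = 32.4, taken as 32.

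**The plan's own figure.** The plan gives no figure for the effect of centre; its only figure is 36 per arm. For 34% versus 4% at 80% power, a two-sided 5% test with continuity correction needs 32 per arm, and 32/0.90 = 35.6, rounded up to 36. The stated one-sided 5% gives 21 per arm, or 24 after attrition (27 and 30 with the correction). That mismatch is a separate matter. Two-sided 5% is used below, with a one-sided check at the end.

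**Assumed, because the documents do not give them.** Centre sizes (8 versus 8 evaluable in each of four centres) and centre-specific risks (three sets, each averaging 34%).

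**Approximation under the null.** Let p_k be the risk in centre k and p̄ their mean.
- Variance used by the pooled test: p̄(1 − p̄) × 2/n
- Variance under the stratified design: mean[p_k(1 − p_k)] × 2/n
- Ratio R = mean[p_k(1 − p_k)] / [p̄(1 − p̄)]
- Actual two-sided size ≈ 2 × [1 − Φ(1.96/√R)]
- Standard error too large by the factor 1/√R

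Here p̄(1 − p̄) = 0.34 × 0.66 = 0.2244.

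| Assumed centre risks | mean p_k(1 − p_k) | R | 1/√R | Approximate size |
|---|---|---|---|---|
| 25/30/38/43% | 0.2196 | 0.978 | 1.01 | 4.8% |
| 15/25/40/56% | 0.2004 | 0.893 | 1.06 | 3.8% |
| 5/20/45/66% | 0.1699 | 0.757 | 1.15 | 2.4% |

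**Simulation** (same risks, no continuity correction, two-sided 5%):

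| Assumed centre risks | Unstratified chi-square | Mantel-Haenszel (CMH) |
|---|---|---|
| 25/30/38/43% | about 5.0% | about 5.0% |
| 15/25/40/56% | 3.9% | 4.9% |
| 5/20/45/66% | 2.5% | 4.9% |

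The approximation and the simulation agree to within a few tenths of a point.

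**Power.** Homogeneous centres at 34% versus 4%: 92.0% unstratified, 91.9% CMH. With an assumed smaller and heterogeneous effect (centre risks of 5-48% versus 1-8%): 63.9% and 65.2%.

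**Check at one-sided 5%, 36 per arm, 9 per arm in each centre.**

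| Assumed null centre risks | Chi-square | CMH | Coverage of unstratified 95% CI |
|---|---|---|---|
| 19% in all | 0.048 | 0.050 | 94.6% |
| 10-28% | 0.046 | 0.051 | 94.9% |
| 5-36% | 0.040 | 0.050 | 95.7% |
| 2-50% | 0.028 | 0.052 | 97.3% |

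Unequal centres (18, 8, 6 and 4 per arm) show the same pattern.

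**Rejecting whenever either test rejects.** The two-sided error is at most about 5.3%; the one-sided error is at most about 0.052.

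**The case against.** The strongest defence is that the choice is disclosed, reasoned and valid. An unadjusted primary analysis followed by a centre-adjusted secondary one is a recognised approach, and the pooled test does not exceed its level to any material extent. The article also describes real steps towards uniformity: one operative protocol, surgeons familiar with it beforehand, a brace instruction meeting in every hospital, and standardised recording of complications. The planned conservative-arm risk of about 4% leaves little room for centres to differ in that arm. With moderate centre differences the loss almost disappears. The 2.5% figure needs a thirteenfold spread in risk (5% to 66%), and the 3.9% figure nearly a fourfold one. All of this stands, and it limits the point to a modest gain.

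Two stronger readings are tempting, and the documents support neither.

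- A reader might infer that the plan lets the data choose the primary analysis. It does not. The Data analysis section fixes the unstratified test as primary without condition and labels Mantel-Haenszel secondary and exploratory. Only whether that secondary analysis is run depends on the data. Even picking the more favourable test every time would barely raise the error rate.
- A reader might infer that the intervals are wrong in a way that produces false positives. The departure caused by ignoring centre is in the conservative direction only.

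It can also be said that the exact trigger for an exploratory analysis belongs in a statistical analysis plan, which is not shown. That is fair, so the missing definition is not counted as a defect in itself. What remains is that the article makes the stratified result conditional when it could simply always be reported.

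**Conclusion.** The point holds in a limited form. The primary analysis sets aside a factor used to stratify randomisation. The consequence is lost precision if centres differ strongly: a size of 3.9% or 2.5% instead of 5% in the two more heterogeneous scenarios, with null standard errors about 6% and 15% too large. It is negligible if centre risks lie within about 25-43%. These sizes rest on assumed centre risks and equal centres of 16. At the planned effect with homogeneous centres, the two methods have practically the same power.

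The conclusion of the trial is not at risk of a false-positive result from this choice, and the sample size is unaffected. The case for change is that it costs almost nothing, not that the present plan is invalid.

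**What to change.** In the Data analysis section:

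1. Make the centre-stratified Mantel-Haenszel (CMH) test the primary test, with the Mantel-Haenszel risk difference and its 95% confidence interval as the primary estimate. The estimate is Σw_k d_k / Σw_k, where d_k is the risk difference in centre k and w_k = n_1k n_0k / N_k.
2. Report the unstratified chi-square as a sensitivity analysis, in all circumstances.
3. Delete the condition that makes the Mantel-Haenszel analysis depend on centre differences appearing.

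The cost is a change of wording. The method is already named in the plan and no more patients are needed. The documents do not show whether the planned software produces the stratified risk difference directly, but it can be computed from the four centre tables.

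If the sponsor prefers to keep the unstratified primary analysis, the minimum change is to report the stratified one every time, without a trigger.
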